## Abstract

**Background:**

Implantable Cardioverter Defibrillator (ICD) therapy has been proven to be beneficial and efficacious for the treatment of serious ventricular tachyarrhythmias in primary prevention patients. However, primary prevention patients appear to have a lower incidence of ventricular arrhythmias in comparison to secondary prevention patients and consequently likely experience a higher proportion of detections due to supraventricular arrhythmias. Recent trials have demonstrated that strategic and specific programming choices reduce the number of inappropriate shocks and that anti-tachycardia pacing (ATP) is an effective alternative to shock therapy for many sustained ventricular arrhythmias.

**Methods:**

The **P**rimary P**re**vention **Par**ameters **E**valuation (PREPARE) study is a multi-center cohort study, evaluating the efficacy of a pre-specified strategic profile of VT/VF detection and therapy settings in 700 primary prevention patients in an effort to safely reduce the number of shock therapies delivered. The patients, both with and without cardiac resynchronization therapy, are compared to a well-qualified set (n = 691) of historical controls derived from the MIRACLE ICD and EMPIRIC trials. This manuscript describes the design of the PREPARE study. The study results, to be presented separately, will characterize the efficacy of this programming set (PREPARE) compared with physician-tailored programming (MIRACLE ICD and EMPIRIC).

## Background

Implantable defibrillator therapy terminates ventricular tachyarrhythmias and improves survival of patients in multiple populations at risk of sudden cardiac death. [1-3] Initially, ICD therapy was applied only to secondary prevention patients: that is, those who had been resuscitated from a cardiac arrest or other sustained ventricular tachyarrhythmias. The impact of other studies, such as MADIT, MUSTT, MADIT II and SCD-HeFT, as well as the CMS national coverage decision in January of 2005, is that the large majority of patients currently receiving ICDs have primary prevention indications and no symptomatic arrhythmias prior to ICD implantation. [4-8]

There are substantial differences in the clinical and rhythm characteristics of patients with primary and secondary prevention indications for ICD therapy. However, it is an important goal to minimize the morbidity of the therapy for all ICD patients. Patients who receive multiple shocks have difficulty adjusting to the ICD implantation, due to increased anxiety and depression. [9,10] In addition, patients who have not had a significant life-threatening arrhythmic experience such as sudden cardiac death may be less accepting of unnecessary shock therapies.

The EMPIRIC and Painfree Rx studies have shown that a standardized set of VT/VF parameters extensively utilizing SVT discriminators and anti-tachycardia pacing (ATP) therapies can be effective in reducing patient shocks after ICD implantation for a mixed population of primary and secondary prevention patients. [11,12] It is the purpose of the PREPARE trial to evaluate strategies specifically designed to reduce shocks in a population of patients with primary prevention ICD indications with and without cardiac resynchronization indications and therapy.

## Methods/Design

### Hypothesis

The PREPARE study examines the hypothesis that a pre-specified strategic profile of tachyarrhythmia detection and therapy parameters is able to reduce the overall morbidity of ICD therapy in patients with primary prevention ICD indications with or without cardiac resynchronization therapy.

#### Morbidity index

The components of the Morbidity Index are:

• Syncope (secondary to tachyarrhythmia or presumed tachyarrhythmia)

• Untreated sustained symptomatic VT/VF events

• Episodes of spontaneous ventricular tachyarrhythmia that result in device-delivered shock

• Episodes that result in an inappropriate device-delivered shock.

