#### Incidence Density (ID)

The Morbidity Index incidence density is calculated by dividing the total number of Morbidity Index events by the total number of years of follow-up. The primary endpoint is the difference in Morbidity Index incidence density between the study patients programmed to the PREPARE settings and the control population programmed to physician-tailored programming.

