### Statistical analysis

The primary endpoint is the difference in Morbidity Index incidence density between the study patients programmed to the PREPARE settings and the control population programmed to physician-tailored programming. The PREPARE programming strategy will be considered superior to the physician-tailored programming approach if a statistically significant reduction in the incidence density is demonstrated in the PREPARE group when compared to the historical control.

There were 347 shocked spontaneous VT/VF episodes, 4 events of arrhythmogenic syncope, and no episodes of untreated symptomatic sustained VT/VF in the 691 control population patients followed for 503 years (ID = 0.70). Assuming that the PREPARE programming strategy results in a 25% reduction in the number of shocked spontaneous VT/VF episodes, the rates of arrhythmogenic syncope and untreated symptomatic sustained VT/VF events remain the same, and the same number of years of follow-up, a total of 700 patients will provide at least 95% power for the primary hypothesis, tested at the two-sided significance level of 0.05. Both the Morbidity Index ID and the secondary analysis of the Morbidity Tachycardia Index ID will be tested using the comparison of incidence rates test. [22]

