## Summary

The PREPARE study evaluates the ability of a pre-specified programming strategy to reduce VT/VF episode-related morbidity using a multi-center, prospective cohort design. The primary prevention population of 700 defibrillator patients with and without resynchronization therapy will be compared to 691 historical control patients. The VT/VF episode-related morbidity is assessed by a primary objective that indexes, for the number of years of follow-up, the total number of shocked spontaneous VT/VF episodes, untreated symptomatic sustained VT/VF episodes, and arrhythmogenic syncopal events.

The use of ICD and CRT+ICD devices in the primary prevention patient population has expanded dramatically over the last five years. Optimal programming for these patients has been investigated by other trials and understanding of these programming options continues to evolve. The programming choices available in the current devices enable additional specificity as it relates to the detection and treatment of ventricular arrhythmias. The PREPARE study results will increase the understanding of how to better develop programming strategies that positively impact primary prevention patients and their caregivers.

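### The primary endpoint is defined two ways: the Morbidity Index counts inappropriate shocks, but the control rate, the power statement and the Summary's primary objective leave them out

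*Protocol article*

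**What the plan says.** The Morbidity index section of the protocol article lists four components. Two of them are shocks, entered as separate items: "Episodes of spontaneous ventricular tachyarrhythmia that result in device-delivered shock" and "Episodes that result in an inappropriate device-delivered shock". The other two are arrhythmia-related syncope and untreated sustained symptomatic VT/VF. The Incidence Density section says the rate is "calculated by dividing the total number of Morbidity Index events by the total number of years of follow-up", and the primary endpoint is the between-group difference in that rate. By these two sections, inappropriate shocks count.

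The Statistical analysis section keeps the name Morbidity Index but describes the control data as follows: "There were 347 shocked spontaneous VT/VF episodes, 4 events of arrhythmogenic syncope, and no episodes of untreated symptomatic sustained VT/VF", over 503 years of follow-up in 691 patients, with a stated rate of 0.70. It gives no count of inappropriate shocks. The planned effect is "a 25% reduction in the number of shocked spontaneous VT/VF episodes", with the assumption that "the rates of arrhythmogenic syncope and untreated symptomatic sustained VT/VF events remain the same, and the same number of years of follow-up". Nothing is assumed about inappropriate shocks.

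The Summary says the primary objective indexes "the total number of shocked spontaneous VT/VF episodes, untreated symptomatic sustained VT/VF episodes, and arrhythmogenic syncopal events" by years of follow-up. Inappropriate shocks are again absent.

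**The concern.** A reader of the endpoint section and a reader of the Summary would count different events for the same primary endpoint. The difference is material for three reasons.

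- **The omitted component is a main target of the intervention.** The Programming section names fewer supraventricular rhythms misread as ventricular among its three strategies. The Discussion gives SVT shocks a section of their own, covering the detection cut-off, the monitor zone, the longer detection duration and the discriminators. Including or excluding inappropriate shocks can change the estimated effect.
- **Rhythm classification decides inclusion under one version only.** The Data collection section says that some MIRACLE ICD episodes had not been classified as true VT or true SVT and would be reviewed by a scientist internal to the sponsor. Under four components, a spontaneous shocked episode counts whichever way it is classified. Under three components read literally, an SVT label removes it from the control numerator. In a single-arm study with historical controls, that should not be left open.
- **Two versions in print leave room to choose after the data are seen.**

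**Working it through.** **Inputs, all from the Statistical analysis section.** Control events: 347 shocked spontaneous VT/VF episodes, 4 syncopes, 0 untreated events. Control follow-up: 503 years. Effect: 25% fewer shocked spontaneous VT/VF episodes, other stated rates unchanged, same follow-up. Two-sided level 0.05; stated power at least 95%.

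**1. Reproduce the stated control rate.**

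(347 + 4 + 0)/503 = 351/503 = 0.698, which rounds to 0.70.

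The three listed counts account for the whole figure. There is no unlisted fourth term.

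**2. Reproduce the power for that count.**

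Expected PREPARE events: 0.75 × 347 + 4 = 264.25.

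With equal follow-up, the two-sample Poisson comparison has z = (351 − 264.25)/√(351 + 264.25) = 86.75/24.80 = 3.497.

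Power = Φ(3.497 − 1.960) = 93.8%.

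Other forms of the test (log rate ratio, square-root transform, exact conditional, continuity-corrected) give 93.3% to 93.9%. This is 1.2 points below the stated 95%, so I treat the figure as approximately reproduced. With 700 years of PREPARE follow-up the same calculation gives 96.5%. So both the rate and the power were evidently worked out from the three-component count.

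**3. Add the missing component.** The article gives no control count of inappropriate shocks, so a range is needed. Suppose the 347 excludes them and they are a share s of all shocked episodes, with s from 20% to 40% (assumption). Total shocked episodes are 347/(1 − s).

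- s = 20%: 347/0.8 = 434, so about 87 inappropriate; rate (434 + 4)/503 = 0.87.
- s = 40%: 347/0.6 = 578, so about 231 inappropriate; rate (578 + 4)/503 = 1.16.

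**4. Power for the four-component endpoint**, by the formula in step 2 with 503 years per group:

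| Assumed inappropriate shocks in controls | Control rate | Power if they also fall 25% | Power if they do not fall |
|---|---|---|---|
| 0 (three-component count) | 0.70 | 93.8% | 93.8% |
| 50 | 0.80 | 96.3% | 90.0% |
| 87 (20% share) | 0.87 | 97.5% | 87.1% |
| 100 | 0.90 | 97.8% | 86.0% |
| 200 | 1.10 | 99.3% | 77.7% |
| 231 (40% share) | 1.16 | 99.5% | 75.2% |
| 347 (50% share) | 1.39 | 99.9% | 66.9% |

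Worked case, 100 extra control episodes that do not fall: control 451, PREPARE 264.25 + 100 = 364.25; z = 86.75/√815.25 = 3.038; power = Φ(1.078) = 86.0%.

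The absolute difference of 86.75 events stays the same in the last column while the variance grows, so power falls. If the added component falls as well, the difference grows faster than its standard error and power rises.

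All these figures treat episodes as independent Poisson events, as the planned comparison of incidence rates does. Whether that is reasonable is a separate question.

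**The case against.** The strongest reply is that this is a labelling fault only. In the Data collection section, the bias called incomplete adjudication of VT/VF episodes turns out to concern episodes not yet classified as true VT or true SVT. The term VT/VF episode may therefore mean an episode the device detected as VT/VF, whatever its true rhythm. The MIRACLE ICD part of the 347 could not have been fully split at planning. On that reading the 347 already includes inappropriate shocks, 0.70 is the four-component rate, and only the wording needs correcting. It can be added that the endpoint section is explicit, that the Statistical analysis section names the Morbidity Index without redefining it, that the Summary is a closing paraphrase, and that the 20% to 40% share has no source in the article.

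Much of this is fair. The reading is possible, the size is conditional, and the direction of any power error is unknown; power drops only if the programming fails to reduce shocks that it is meant to reduce. But the article never says that the 347 includes SVT shocks. The Morbidity index section lists the two kinds of shock apart, and the Data collection section itself lists VT/VF and SVT episodes as different things. If the benign reading is right, the label in the Statistical analysis section and the objective in the Summary are still wrong against the definition. Nor is this detail left to a fuller protocol: the article states the components in one place and states them differently in two others.

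**Conclusion.** The inconsistency stands and must be corrected, because it concerns what the primary endpoint counts. The definition has four components; the control rate, the power statement and the Summary's primary objective use three.

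Its size depends on a number the article does not give. If the 347 already includes inappropriate shocks, the control rate is unaffected and the fault is one of wording. If it excludes them, 0.70 understates the control rate of the defined endpoint, and the 25% effect applies to only part of the index. The stated power of at least 95% then cannot be attributed to that endpoint without the missing count and an assumed effect on inappropriate shocks.

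**What to change.** 1. Keep the four-component list in the Morbidity index section as the only definition of the primary endpoint, and reword the Statistical analysis and Summary sections to match it.
2. Report control events by component: appropriate shocks, inappropriate shocks, syncope, untreated VT/VF. State explicitly whether the 347 includes inappropriate shocks.
3. Restate the control rate and power for the four-component endpoint, with the assumed reduction in inappropriate shocks stated. If the 347 already includes them, a corrected label suffices for the rate, together with a statement that the 25% reduction applies to both kinds of shock.
4. Report appropriate and inappropriate shock rates separately as components of the result.

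The cost is wording plus a recount of control data already held. The split by component depends on the true VT/true SVT review of unclassified MIRACLE ICD episodes, which the article already plans to complete before the study ends. Enrolment does not change; the restated power serves to describe the study correctly.

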#### Incidence Density (ID)

The Morbidity Index incidence density is calculated by dividing the total number of Morbidity Index events by the total number of years of follow-up. The primary endpoint is the difference in Morbidity Index incidence density between the study patients programmed to the PREPARE settings and the control population programmed to physician-tailored programming.

### Secondary endpoint

#### Morbidity Tachycardia Index

The key secondary endpoint is the difference in Morbidity Tachycardia Index incidence density, which adds anti-tachycardia pacing events to the Morbidity Index as a reflection of all tachycardia events, between patients programmed to the PREPARE settings and the control population.

### Design

The PREPARE study is a prospective, single arm, multi-center cohort study designed to evaluate the efficacy of a pre-specified strategic profile of VT and VF detection and therapy settings designed for ICD indicated patients with no history of spontaneous sustained symptomatic VT or VF. All study patients received a Medtronic Marquis family ICD system with or without capacity for cardiac resynchronization implanted between October 2003 and April 2005. Approximately 700 patients were enrolled in the United States and the Netherlands and were programmed to the PREPARE parameters and followed for endpoints for 12 months after PREPARE programming.

For the purposes of this study, primary prevention patients are defined as those patients indicated for ICD or CRT + ICD implantation without a baseline history of ventricular fibrillation, ventricular flutter, monomorphic VT, polymorphic VT, or Torsades de Pointes. Patients may have a history of cardiovascular syncope, since the PREPARE findings are intended to be generalized to the primary prevention patient population seen in clinical practice.

• Inclusion criteria required:

○ Initial implantation for primary prevention ICD indications or

○ Prior ICD implantation within 6 months without subsequent

spontaneous VT/VF episodes

• Patients were excluded for:

○ History of spontaneous sustained symptomatic ventricular arrhythmias,

○ An electrophysiology test in the past, with sustained inducible VT < 180 bpm,

○ Any ICD implanted greater than 6 months prior to the study,

○ An ICD implanted within the previous 6 months, with subsequent history of a spontaneous episode of VT or VF appropriately treated with either ATP or shock.

○ Heart transplant

○ Mechanical right heart valve.

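### The crude rate comparison does not align PREPARE and control follow-up on time since implant, so timing can bias the primary result by an unknown amount and in an unknown direction

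*Protocol article*

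**What the plan says.** All references are to the protocol article.

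- **PREPARE window (Design).** Patients are "followed for endpoints for 12 months after PREPARE programming". The clock starts at programming. Patients with an existing device are eligible under "Prior ICD implantation within 6 months without subsequent" spontaneous VT/VF episodes, so programming can fall anywhere from 0 to 6 months after implant.
- **Control window (Statistical analysis).** The only figures are the totals: "691 control population patients followed for 503 years (ID = 0.70". The article does not say whether control time starts at implant, at randomisation or at another visit, nor how follow-up is spread across patients.
- **Estimator (Incidence Density).** The rate is obtained by "dividing the total number of Morbidity Index events by the total number of years of follow-up", and the two rates are compared with a two-sample incidence rate test.
- **Planning assumption (Statistical analysis).** The power statement assumes "the same number of years of follow-up" as in the controls.
- **Named biases (Data collection).** Two are discussed: how adverse events were collected, and incomplete adjudication of episodes. The follow-up window is not among them.

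**The concern.** Dividing by person-years handles follow-up of different length only when the event rate is flat over the period observed. If the rate changes with time since implant, a crude rate is an average weighted by where each cohort's person-time falls. Here the weights differ by design: PREPARE time may extend to month 18 after implant, while the average control contributes under 9 months.

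If shocks are more frequent soon after implant, controls carry relatively more of the high-rate period and PREPARE relatively more of the quieter one. If the rate rises with time, the bias runs against PREPARE. With no concurrent control arm, the planned test cannot separate either effect from the effect of programming.

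This is distinct from baseline imbalance and from the requirement that late entrants be free of VT/VF episodes since implant. It would remain if both of those were dealt with.

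**Working it through.** **Inputs from the article.** Controls: 691 patients, 503 years, "347 shocked spontaneous VT/VF episodes, 4 events of arrhythmogenic syncope, and no episodes of untreated symptomatic sustained VT/VF". Planned effect: 25% fewer shocked episodes, syncope unchanged. Two-sided alpha 0.05. PREPARE: 700 patients, 12 months.

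**Step 1. The plan's own figures.** Control rate = (347 + 4 + 0)/503 = 351/503 = 0.698, matching the stated 0.70. Planned PREPARE events on 503 years = 0.75 × 347 + 4 = 264.25, a rate of 0.525.

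- 503 years per group: SE = √(0.698/503 + 0.525/503) = 0.0493; power = Φ(0.1725/0.0493 − 1.96) = 93.8%.
- 700 PREPARE years: SE = √(0.698/503 + 0.525/700) = 0.0462; power = Φ(0.1725/0.0462 − 1.96) = 96.2%.

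The stated power of at least 95% lies between the two, so power is not the problem.

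**Step 2. The windows.** Control mean = 503/691 = 0.728 year = 8.7 months. PREPARE as designed = 12 months, so up to 700 years. The power statement's 503 years over 700 patients would be 8.6 months each, which does not fit the planned 12. The full 12 months is 700/503 = 1.39 times the control person-time, an upper limit that ignores death and withdrawal.

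**Step 3. Timing-only rate ratio.** Assumptions not in the article: control time starts at implant; every control is followed for at least 3 months; the rate in months 0-3 is *k* times the later rate; programming has no effect; PREPARE follow-up is complete.

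- Control mean rate, relative to the later rate: C = 1 + (k − 1) × 3/8.735
- PREPARE mean rate, with a share *s* entering at month 3: P = 1 + (k − 1) × (3/12) × (1 − s)
- Spurious reduction = 1 − P/C

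| k | C | P, s = 0 | Reduction | P, s = 20% | Reduction |
|---|---|---|---|---|---|
| 1 | 1.000 | 1.000 | 0% | 1.000 | 0% |
| 1.5 | 1.172 | 1.125 | 4% | 1.100 | 6% |
| 2 | 1.343 | 1.250 | 7% | 1.200 | 11% |
| 3 | 1.687 | 1.500 | 11% | 1.400 | 17% |

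**Step 4. Against the significance threshold.** Treating events as independent, the smallest significant observed reduction solves (λ0 − λ1)/√(λp(1/Y0 + 1/Y1)) = 1.96, with λp the pooled rate.

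- 503 PREPARE years: about 301 events against 351, since (351 − 301)/√652 = 1.96. The reduction is about 14%.
- 700 PREPARE years: rate 0.606 (424 events), λp = 775/1203 = 0.644, SE = 0.0469, 0.092/0.0469 = 1.96. The reduction is about 13%.

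The chance of a significant reduction with no programming effect is Φ(−ln(P/C)/√(1/351 + 1/e) − 1.96), where e = 0.698 × 700 × P/C. For k = 2 and s = 0: e = 454.5 and Φ(0.072/0.0711 − 1.96) = 17%. For k = 1.5 and 3 with s = 0 it is 8% and 37%. The nominal value is 2.5%.

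**Step 5. Relaxing the assumptions.**

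- *Control time starts 1 month after implant.* C = 1 + (k − 1) × 2/8.735. For k = 2, C = 1.229; with s = 0 the ratio is 1.25/1.229 = 1.02, so the bias has gone and slightly reversed (1.01 for k = 1.5, 1.03 for k = 3). The break-even offset is 3 − 8.735/4 = 0.8 month. With s = 20%, reductions of about 1%, 2% and 4% remain for k = 1.5, 2 and 3.
- *PREPARE mean follow-up 10.5 months through dropout.* For k = 2 and s = 0, P = 1 + 3/10.5 = 1.286; 1.286/1.343 = 0.957, so the reduction falls from 7% to 4%.
- *Early rate lower (0.67 times the later rate for 3 months), s = 0.* Ratio = (1 − 0.33 × 0.25)/(1 − 0.33 × 0.343) = 0.9175/0.887 = 1.035, so PREPARE looks about 3.5% worse.

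**The case against.** The strongest reply is that incidence density exists to handle unequal follow-up, that no falling rate is documented, and that the controls' time origin is not given, so the mismatch of windows is itself inferred. Starting controls about 1 month after implant cancels the effect when all PREPARE patients start at implant. Controls followed for under 3 months, or PREPARE dropout, would shrink it. All of this stands, and it makes the bias conditional in existence, size and direction.

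It does not remove the point. The same missing facts mean the article gives no ground for treating the crude comparison as fair.

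It can also be said that stratifying person-time is detail for a full analysis plan. However, the article itself fixes the time origin for PREPARE, the rate formula and the test, and it discusses the biases of the historical comparison without this one.

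Two stronger readings should be resisted. A reader might infer that timing alone could supply an entire significant reduction. Of the six scenarios with k above 1, only one exceeds 13-14% (k = 3 with 20% entering at month 3, giving 17%), and neither input is in the article. A reader might also take the equal-years assumption in the power statement as evidence of bias. It is a planning assumption at odds with the 12-month design, and longer PREPARE follow-up only raises power.

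**Conclusion.** The concern holds as a conditional one. The article fixes a PREPARE window of 12 months from programming, with entry 0 to 6 months after implant, and compares it by a crude rate with controls averaging 8.7 months from an unstated origin. Validity needs either a constant rate or matching windows, and the article establishes neither.

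Under the assumptions of Step 3, timing lowers the PREPARE rate by 4-11% with everyone starting at implant and by 6-17% with 20% entering at month 3. That is material beside a threshold of 13-14%, but the range depends on a falling rate and on controls starting at implant. The documents do not show that timing favours PREPARE. The change is worth making before analysis because it is cheap and the design has no concurrent arm to absorb the effect.

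**What to change.** 1. State the time origin of control follow-up in each of the two source trials.
2. Index events and person-time by time since implant in all three cohorts, with prior-implant PREPARE patients entering at their programming date.
3. Estimate the primary rate ratio stratified by post-implant interval (for example 0-3, 3-6 and 6-12 months) over the window that both cohorts cover.
4. Report the crude incidence density alongside.
5. Add a sensitivity analysis limited to PREPARE patients programmed at implant.
6. Reconcile the equal-years assumption in the power statement with the planned 12 months.

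The cost is analysis wording and the use of implant, programming and last-follow-up dates. The article does not say that these are held for every control, so availability must be checked and any gaps reported. A little late PREPARE follow-up is lost from the primary comparison. If the rate proves constant, the estimate should barely move and the crude result is better defended.

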The EMPIRIC study was a multi-center randomized trial of 900 ICD patients, designed to compare standardized vs. physician-tailored VT/VF programming in both primary and secondary prevention patients. [11] The study was recently completed, and its patient population is thought to better reflect the higher ratio of ICD implant indications seen during enrollment into the PREPARE study than the MIRACLE ICD Trial, reported in 2003. [13] Additionally, there were a large number of patients (276) randomized in the EMPIRIC Trial to the physician-tailored arm who met the PREPARE Trial definition of primary prevention. These patients, along with the 415 primary prevention patients from the MIRACLE ICD Trial, have been combined, producing a total of 691 patients in the historical control sample.

When compared with PREPARE patient baseline demographics, the patient characteristics of the combined physician-tailored arm are not clinically different. The baseline clinical data for the study and control patients is listed in Table 1. This table includes baseline demographics which were collected in PREPARE, MIRACLE ICD and EMPIRIC. Demographics for MIRACLE ICD and EMPIRIC are shown separately and in combination.

**Table 1 T1:** Patient Demographics

	**PREPARE Patients** ** (N = 700)**	**MIRACLE ICD Patients** **(N = 415)**	**EMPIRIC Patients** **(N = 276)**	**Combined Control (MIRACLE ICD and EMPIRIC) Patients** **(N = 691)**

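### PREPARE's event-free and non-inducibility criteria have no stated counterpart in the historical controls, so eligibility differences can lower the PREPARE rate without any programming effect

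*Protocol article*

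**What the plan says.** The Design section defines a primary prevention patient by baseline history: no VF, flutter, monomorphic or polymorphic VT, or torsades. It then adds separate eligibility criteria for PREPARE. A patient with a prior implant must have received it within 6 months and must have had no spontaneous VT/VF since. Among the exclusions are "An ICD implanted within the previous 6 months, with subsequent history of a spontaneous episode of VT or VF appropriately treated" by ATP or shock, and "An electrophysiology test in the past, with sustained inducible VT < 180 bpm". Follow-up is 12 months from PREPARE programming.

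For the controls, the Control population section states one filter. MIRACLE ICD contributes 415 primary prevention patients. EMPIRIC contributes 276 patients "randomized in the EMPIRIC Trial to the physician-tailored arm who met the PREPARE Trial definition of primary prevention". The text refers to the definition, not to the inclusion and exclusion criteria.

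The Statistical analysis section compares Morbidity Index incidence density between the cohorts by a comparison of incidence rates test and states no adjustment. The Control population section recognises case-mix bias from less advanced heart failure and adds EMPIRIC to address it. The Data collection section names two further sources of bias, both about how events were collected and adjudicated. Neither section discusses a difference in eligibility.

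**The concern.** Screening prior-implant patients for freedom from VT/VF selects on the same kind of event that the endpoint counts: shocked VT/VF episodes make up 347 of the 351 control events used for planning. If patients differ in their underlying rates, those who have stayed event-free have a lower expected rate afterwards. Excluding sustained inducible VT below 180 bpm plausibly works in the same direction. If only PREPARE is screened, part of any observed reduction comes from who was admitted rather than from how the devices were programmed. Balancing the Table 1 characteristics would not fully remove this, because the selection is on arrhythmia history itself. At stake is whether a significant result can be attributed to the programming.

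**Working it through.** **1. The plan's own figure.** Inputs from Statistical analysis: "There were 347 shocked spontaneous VT/VF episodes, 4 events of arrhythmogenic syncope, and no episodes of untreated symptomatic sustained VT/VF"; 691 controls followed for 503 years; "Assuming that the PREPARE programming strategy results in a 25% reduction in the number of shocked spontaneous VT/VF episodes"; "tested at the two-sided significance level of 0.05". I assume a standard two-sample Poisson rate test.

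- Control: (347 + 4 + 0)/503 = 351/503 = 0.698 per year, which matches the stated 0.70.
- PREPARE: (0.75 × 347 + 4)/503 = 264.25/503 = 0.525 per year, a rate ratio of 0.753.
- Power with 503 years per group is 93.8%. With 700 PREPARE years (12 months each) it is 96.2–96.7%, depending on the form of the test. The stated figure of at least 95% therefore reproduces to within about 2 points.

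**2. How large a deficit the test would call significant.** With no programming effect and a PREPARE rate lowered by a fraction x, z = (r0 − r1)/√[r̄(1/T0 + 1/T1)], where r1 = r0(1 − x) and r̄ is the pooled rate. At expected counts, z reaches 1.96 at x = 14.3% with 503 years per group, and at x = 13.2% with 700 PREPARE years. The chance of a significant result favouring PREPARE is:

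| Deficit from selection | 503 years each | 700 PREPARE years |
|---|---|---|
| 0% | 2.5% | 2.5% |
| 5% | 9.9% | 10.9% |
| 10% | 27.4% | 31.5% |
| 15% | 54.2% | 61.0% |
| 20% | 79.8% | 85.6% |

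These chances assume Poisson counts. Variation between patients of the kind used in step 3 would change them.

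**3. What an event-free wait could do.** Let patient rates vary around μ = 347/503 = 0.69 per year with gamma variance θ (relative to a mean of 1). After an event-free time t, the expected rate is multiplied by 1/(1 + θμt). If a share f of PREPARE entered this way, the overall fall is f × [1 − 1/(1 + θμt)]. The document gives none of f, t and θ, so all three are assumptions.

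| f | t | θ | Overall fall |
|---|---|---|---|
| 10% | 1 month | 4 to 10 | 1.9% to 3.7% |
| 20% | 3 months | 1 | 2.9% |
| 20% | 3 months | 4 | 8% |
| 20% | 6 months | 10 | 16% |
| 40% | 3 months | 4 | 16% |
| 40% | 6 months | 10 | 31% |

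The 6-month rows are extreme, since 6 months is the maximum permitted. Each patient's rate is held constant over time, so the model does not need a higher rate early after implant.

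**4. Adding the inducibility exclusion.** Let s be the rate reduction in prior-implant patients, g the share of controls with slow inducible VT, and h their rate ratio. The combined deficit is 1 − (1 − fs)/[1 + g(h − 1)]. All inputs are assumed.

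- Low (f 5%, s 10%, g 2%, h 1.5): 1 − 0.995/1.01 = 1.5%; chance of a false positive 3.9%.
- Middle (f 10%, s 25%, g 5%, h 2): 1 − 0.975/1.05 = 7.1%; 16.0%.
- High (f 30%, s 50%, g 10%, h 3): 1 − 0.85/1.20 = 29%; 98.7%.

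**5. Effect on interpretation.** If the observed rate ratio were the planned 0.753 and selection accounted for 10%, the programming effect would be 1 − 0.753/0.90 = 16%, not 25%.

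**The case against.** The strongest reply is that this rests on what a condensed article leaves unsaid. The full protocol may apply PREPARE's criteria to the controls, and the source trials had eligibility rules not shown here. That limits the claim to what is stated. It does not answer it entirely, because the article does state the control filter and does discuss bias, without mentioning eligibility.

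Second, the definition may already close part of the gap. A control with VT/VF between implant and that trial's baseline has a baseline history and fails the definition. This stands. What remains depends on whether control follow-up starts nearer to implant than it does for prior-implant PREPARE patients, and the article does not give control time zero. Nor does it say whether monomorphic VT in the definition covers induced VT, although listing the electrophysiology exclusion separately suggests that it does not.

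Third, the screen is on VT/VF, while the Morbidity Index also counts inappropriate shocks, which it selects only indirectly. This also stands, and it reduces the effect on the whole index.

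Fourth, the net direction of all differences is unsettled. PREPARE has more ischemic cardiomyopathy (69.7% against 57.0%), and its diary is expected to raise recorded syncope. But it also has a higher mean ejection fraction (27.7% against 24.7%) and more NYHA class I (16.7% against 5.2%). Other biases in either direction do not remove this one.

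Two further inferences are tempting and fail. The difference between a mean control follow-up of 503/691 = 0.73 years and PREPARE's planned 12 months is not in itself a bias, because incidence density divides by years of follow-up. And the inclusion line (no VT/VF since implant) does not conflict with the exclusion line (treated VT/VF only): a patient must pass both, so the narrower line is merely redundant.

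**Conclusion.** The concern holds in a limited form. As stated, PREPARE's eligibility is stricter than the control filter in two respects, both tending to favour PREPARE, and the planned comparison has no stated means of removing the difference. The effect on incidence density runs from about 1–4% to about 30% under assumed shares, waiting times and rates. A deficit of about 13–14% would be enough for significance without any programming effect.

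A reader might go further and conclude that selection alone does lower the PREPARE rate. The document does not support that. It gives neither the share of prior-implant patients, their time since implant, the control time zero, nor the prevalence of slow inducible VT, so the true effect could be trivial. Nor does it support a claim that the time soon after implant is especially rich in events. The conclusion is that the bias is possible, plausible in direction, unquantified, and cheap to address.

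**What to change.** - Apply to the 691 controls every PREPARE eligibility criterion their records support, including sustained inducible VT below 180 bpm and any spontaneous VT/VF between implant and the start of counted follow-up. Report how many controls each criterion removes and which criteria could not be checked.
- State when control follow-up starts, and align time zero relative to implant in both cohorts.
- Pre-specify a comparison limited to PREPARE patients programmed at initial implant, and report the share of the 700 who had a prior implant. This comparison removes the event-free wait but not the inducibility difference, so the first step is still needed.
- Add differing eligibility to the sources of bias discussed under Data collection.

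The cost is re-derivation of the control set from records already assembled, some loss of person-years in both groups, and somewhat wider intervals. Where control records hold no electrophysiology results, that part of the difference remains and should be reported as a limitation.
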